#### Changes in brain function

3.8.2.

fMRI images of all patients will be acquired using a 3.0 T superconducting magnetic resonance scanner (Siemens Medical, Erlangen, Germany) before and after the intervention. All participants will be instructed to keep their eyes closed and bodies aplanatic, and not to think or fall asleep during scanning. The scanning procedure will include a T1 – weighted imaging (T1WI) and BOLD-fMRI. The scanning parameters will be as follows: (1) T1WI: repetition time (TR)/echo time (TE)/T1 = 2000 ms/30 ms/900 ms, field of view (FOV) = 240 mm × 240 mm, voxel size = 0.9 mm × 0.9 mm × 0.9 mm, matrix = 256 × 256, flip angle (FA): 8°, and slice thickness: 0.9 mm; (2) BOLD-fMRI: TR/TE = 2000 ms/30 ms; matrix = 64 × 64, FOV = 240 mm × 240 mm, voxel size = 3.8 mm × 3.8 mm × 4.4 mm, FA = 90°, and slice thickness = 4.4 mm.

#### Changes in gut microbiota

3.8.3.

Faecal samples of all patients will be collected at the beginning and end of the intervention. In the morning, participants will be requested to collect mid-medial faecal samples (at least 2 g) using a disposable stool kit. After the samples are obtained, they will be stored at − 20°C freezers, sent to the laboratory, and placed in the refrigerator at −80°C within 24 h for preservation. We will use a metagenomic sequencing technique to determine the gut microbiota of participants. The DNA of gut microbiota from faecal samples will be extracted using the kit. Subsequently, we will establish a DNA library (paired-end; insert length 350 bp of each sample) according to the manufacturer instructions of Illumina, and conduct high-throughput sequencing using paired-end readings of length 2 × 100 bp. Subsequently, cluster analysis, assembly and annotation of metagenomic data will be conducted. Finally, the annotation, composition, differences, and comparison of species in the intestinal microbiota of patients will be analysed, and the similarities and differences in the diversity and abundance of gut flora will be compared between the AG and WG.

#### Expression of inflammatory cytokines

3.8.4.

Fasting blood samples of all patients will be collected at the beginning and end of the intervention. After obtaining the samples, a serum sample from the participants will be collected using sterile storage tubes; next, we will weigh 500 μL serum sample per tube using a sterilised centrifuge tube, and obtain multiple tubes of each sample for backup. The collected sample will be stored at − 20°C freezers, sent to the laboratory, and placed in the refrigerator at − 80°C within 24 h. Human serum tumor necrosis factor-α (TNF-α), interleukin-1*β* (IL-1*β*), interleukin-4 (IL-4), interleukin-6 (IL-6), interleukin-10 (IL-10), interleukin-18 (IL-18), cyclooxygenase-1 (COX-1), and cyclooxygenase-2 (COX-2) enzyme-linked immunosorbent assay (ELISA) kit will be used for detection.

#### Others

3.8.5.

Drug use, health education completion, acupuncture expectation and treatment satisfaction will be evaluated for patients at the beginning and end of the intervention.

### Safety assessments

3.9.

Physical examinations and vital sign tests are required for all participants. If any adverse events (AEs) occur, a detailed record will be made, the participant will receive appropriate treatment immediately, and the cause of the AEs will be analysed. Most AEs after acupuncture are mild, including the sensation of soreness and distention or localised ecchymoma and bruising that disappear after rest and pressing. Serious AEs will be reported to the ethical committee of the Affiliated Hospital of Chengdu University of TCM in time. When an AE occurs, participants will decide whether or not to quit the trial based on their own will.

### Quality control, data management, and monitoring

3.10.

Before the implementation of this trial, a clinical study manual will be developed, and all investigators will receive specialised training to familiarise them with the clinical study protocol and ensure consistency in the evaluation of efficacy outcomes. Additionally, acupuncture procedures will be stipulated to ensure the accuracy of the acupuncture technique, and acupuncturists will be supervised irregularly. The case report forms will retain all original data of patients and be stored in a secure and restricted access environment. The data will then be entered into a pre-designed, password-protected electronic database by an investigator unaware of the group assignments. Only designated members of the research team will have access to the database. To ensure privacy, all study research documents will be stored in a cabinet in a locked office in Chengdu. The ethical committee of the Affiliated Hospital of Chengdu University of TCM may inspect the study records and monitor the trial.

### Statistical analysis

3.11.

Data analysis will be performed using IBM SPSS version 21.0 (IBM Corp, New York). All data of clinical symptom outcomes will be analysed according to the intention to treat population. The Chi-Square test/Fisher’s Exact test will be used to analyse and count data. Continuous variables as means ± standard deviation or median (± interquartile range), and categorical variables as the number and percentage of participants.

The measurement data includes various scale scores, indicators of brain function, DNA library of gut microbiota, and expression levels of inflammatory cytokines. After exploratory analyses, for variables with normal distribution, independent samples *t*-test will be used for inter-group comparison, and paired samples *t*-test will be used for intra-group comparison. The Mann–Whitney U test will be used for non-normal distributed variables. The correlation analysis between clinical efficacy, gut microbiota, inflammatory cytokines, and brain function will be conducted using multiple linear regression analysis. *p* < 0.05 will be considered the threshold for statistical significance.

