**Methods and design:**

This is a prospective, parallel, multicenter randomized controlled trial. A total of 40 patients with aMCI will be randomly assigned to an acupuncture group (AG) or a waiting-list group (WG), participants in both groups will receive health education on improving cognitive function at each visit, and acupuncture will be conducted twice a week for 12 weeks in the AG. Another 20 matched healthy volunteers will be enrolled as normal control. The primary outcome will be the change in Alzheimer’s Disease Assessment Scale-cognitive scale score before and after treatment. Additionally, functional magnetic resonance imaging data, faeces, and blood will be collected from each participant to characterize the brain function, gut microbiota, and inflammatory cytokines, respectively. The differences between patients with aMCI and healthy participants, and the changes in the AG and WG groups before and after treatment will be observed. Ultimately, the correlation among brain function, gut microbiota, inflammatory cytokines, and clinical efficacy evaluation in patients with aMCI will be analyzed.

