### Primary outcome

3.7.

Changes in the Alzheimer’s Disease Assessment Scale-cognitive (ADAS-cog) score, assessed from the baseline to end of treatment, will be used to evaluate the cognitive function of patients. The ADAS-cog is designed as a rating scale for the severity of cognitive dysfunction in people with AD and comprises 12 subscales designed to assess several cognitive domains, including word recall and recognition, naming, instruction, language comprehension and expression, orientation, praxis, attention and other cognitive abilities. The total score is the sum of the scores of all subscales, with higher scores indicating greater cognitive impairment.

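### The AG-versus-WG comparison of ADAS-cog is not adjusted for baseline: the planned t-test is valid but less precise than ANCOVA, and the within-arm paired tests should be descriptive only

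*Protocol article*

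**What the plan says.** Section 3.7 defines the primary outcome as the change in ADAS-cog: "score, assessed from the baseline to end of treatment, will be used to evaluate the cognitive function of patients". The abstract puts it as "The primary outcome will be the change in Alzheimer’s Disease Assessment Scale-cognitive scale score before and after treatment" and adds that "the changes in the AG and WG groups before and after treatment will be observed". Table 1 schedules ADAS-cog at baseline and week 12 for all patients with aMCI. Section 3.5 sets 20 per group.

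Section 3.11 gives one rule for all measurement data, scale scores included. For normal variables, "independent samples *t*-test will be used for inter-group comparison" and "paired samples *t*-test will be used for intra-group comparison". Otherwise, "The Mann–Whitney U test will be used for non-normal distributed variables". A p-value below 0.05 "will be considered the threshold for statistical significance", with no distinction between the two kinds of comparison. Regression appears only for relating clinical efficacy to the biomarkers, which "will be conducted using multiple linear regression analysis"; it is not used for the treatment effect. The section does not say whether the between-group t-test is on change or on week-12 scores.

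**The concern.** Two things are at stake.

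- **Precision.** In a trial of 40 patients, the baseline value of the primary scale is usually the best available predictor of its week-12 value. A change score uses the baseline with its coefficient fixed at 1. Unless the true slope is close to 1, this adds noise and lets a chance baseline difference between the arms leak into the treatment contrast through regression to the mean. ANCOVA estimates the slope and removes most of both effects at no cost in data.
- **Interpretation.** Both arms receive health education on cognition at each visit, and both repeat the ADAS-cog. Some improvement in both arms is therefore plausible without any effect of acupuncture. Paired tests in each arm, at the same threshold as the between-arm test, can give a significant result in one arm and not in the other when the arms do not truly differ.

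**Working it through.** **Inputs.** From the document: n = 20 per arm, N = 40, threshold 0.05 (taken as two-sided; sidedness is not stated). Section 3.5 bases the sample size on precedent and gives no effect size, SD or power, so there is no planned figure to reproduce. Assumed: raw SD = 1 at both visits; baseline to week-12 correlation ρ between 0.5 and 0.9.

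**1. Variance of the between-arm contrast.** Per patient, the change score has variance 2(1−ρ) and the ANCOVA residual has 1−ρ². The large-sample ratio is (1−ρ²)/[2(1−ρ)] = (1+ρ)/2. Estimating k covariate slopes inflates the ANCOVA variance by 1 + k/(N−k−3). For baseline alone this is 1 + 1/36 = 1.028. For baseline plus three centre terms (four sites) it is 1 + 4/33 = 1.121, here assuming that centre is not prognostic.

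| ρ | (1+ρ)/2 | × 1.028 | 40 ÷ ratio | × 1.121 (with centre) |
|---|---|---|---|---|
| 0.5 | 0.75 | 0.77 | 52 | 0.84 |
| 0.7 | 0.85 | 0.87 | 46 | 0.95 |
| 0.8 | 0.90 | 0.925 | 43 | 1.01 |
| 0.9 | 0.95 | 0.98 | 41 | 1.07 |

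**2. If the t-test is on week-12 scores only.** The comparator variance is 1, so the ratio is (1−ρ²) × 1.028 = 0.77, 0.52, 0.37 and 0.20 at ρ = 0.5, 0.7, 0.8 and 0.9.

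**3. Power.** These are simulations with 20,000 trials per scenario and an assumed true difference of 0.5 raw SD.

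| ρ | t-test on week-12 score | t-test on change | ANCOVA |
|---|---|---|---|
| 0.5 | 34% | 34% | 42% |
| 0.7 | 34% | 51% | 56% |
| 0.8 | 34% | 68% | 71% |

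With no true difference, all three tests rejected in about 5% of trials.

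**4. Chance baseline imbalance.** The SE of the baseline difference is √(2/20) = 0.316 SD. An imbalance of that size moves the expected change-score contrast by (1−ρ) × 0.316 = 0.158, 0.095 and 0.063 SD at ρ = 0.5, 0.7 and 0.8. The SE of that contrast is √[0.2(1−ρ)] = 0.316, 0.245 and 0.200, so the shift is 0.50, 0.39 and 0.32 of a standard error.

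**5. Within-arm tests.** Let both arms have the same true improvement, expressed in SD of change. Let p be the probability that a paired t-test with n = 20 shows significant improvement (noncentral t, 19 df). The probability that AG is significant and WG is not is p(1−p).

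| Equal shift | p | p(1−p) |
|---|---|---|
| 0 | 0.025 | 2% |
| 0.1 | 0.06 | 6% |
| 0.2 | 0.13 | 12% |
| 0.3 | 0.25 | 19% |
| 0.5 | 0.56 | 25% |
| 0.6 | 0.72 | 20% |
| 0.8 | 0.92 | 7% |
| 1.0 | 0.99 | 1% |

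The quantity p(1−p) cannot exceed 25%, so shifts of 0.3 to 0.6 SD lie around its peak.

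**The case against.** The strongest reply is that nothing here is an error. Under randomisation the change-score t-test is unbiased and holds its type I error. Bias given the observed imbalance is a conditional property, not a failure of the test. This stands, and the point is therefore one of efficiency.

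A reader might go further and infer that the plan throws the baseline away. The documents do not support that: section 3.7 and the abstract define the outcome as change, and a change score uses every baseline value. It would be true only of a t-test on week-12 scores, which section 3.11 neither states nor rules out.

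A reader might also infer that a significant paired test in AG would count as proof of efficacy. No section says so. Section 3.11 lists the between-group comparison first, section 3.8.3 compares AG with WG, and the Discussion plans to examine changes between the two groups. What remains is that section 3.11 puts both kinds of test under one threshold without ranking them.

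The gain from adjustment is also modest: it nearly disappears at ρ = 0.9, and three centre terms can cancel it at ρ = 0.8. That limits the size of the point and shapes the remedy. Finally, one may say that such matters belong in an analysis plan that is not shown. But section 3.11 does not leave the method open; it prescribes an unadjusted test, and a plan that follows it inherits the weakness.

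**Conclusion.** The point holds as a recommendation to improve the analysis, not as a finding of invalidity. Against a t-test on change, ANCOVA would cut the variance by about 7% to 23% for ρ between 0.8 and 0.5, and by about 2% at ρ = 0.9. Against a t-test on week-12 scores, the cut would be about 23% at ρ = 0.5 and 63% at ρ = 0.8. The correlation is an assumption throughout, because the document gives none. The range also assumes equal variances at the two visits and a linear relation.

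The risk of misreading the paired tests is real but depends on the common improvement: about 19% to 25% for equal shifts of 0.3 to 0.6 SD of change, 2% to 12% for 0 to 0.2 SD, and 1% to 7% for 0.8 to 1.0 SD. These are probabilities of a pattern of results, not of a decision that the plan prescribes.

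**What to change.** - State one primary analysis: ANCOVA of week-12 ADAS-cog on arm with baseline ADAS-cog as covariate, two-sided 0.05, reporting the adjusted AG−WG difference with its 95% CI.
- Do not add centre terms by default; with 40 patients they can cancel the gain.
- Use the same model for the other scales and the serum markers where the residuals are acceptable. For clearly skewed outcomes, use a transformed or rank-based baseline-adjusted version in place of the unadjusted Mann–Whitney test.
- Report within-arm before/after changes as description, and say that they carry no efficacy claim.

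The cost is a change of wording, best made before the group codes are opened. No extra data, visits or patients are needed, and the SPSS package named in section 3.11 fits ANCOVA.

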### Sample size

3.5.

Previous studies (34, 35) have suggested that 15 participants should be included in each group to ensure a stable statistical effect for brain fMRI data analysis. In most similar studies (36–38) which used fMRI, gut microbiota, or inflammatory cytokines as indicators to explore the mechanisms of acupuncture, the sample size was mostly 15–20 participants per group. Thus, the sample size in our study will be 20 participants per group. Additionally, 20 healthy participants will be included.

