#### Changes in clinical symptoms

3.8.1.

The following clinical efficacy-related outcomes in patients with aMCI will be used for this study: improvement of cognition, daily living ability, mental behaviour, emotion, and sleep. These outcomes will be measured at baseline and after 12 weeks of the intervention. Each participant will be evaluated by a professional physician unaware of the intervention regimen. Medication combination, compliance, dropout, and elimination cases will be recorded.

The Auditory Verbal Learning Test – Huashan version (AVLT-H) scale will be adopted to evaluate the memory function of patients. It is an objective test proven to be a sensitive measure for diagnosing aMCI (40). The word list consists of 12 two-character Chinese words from three semantic categories (flowers, occupations, and apparel), with four words in each category. The AVLT-H score is allocated as follows: (1) the immediate recall total score representing verbal working memory; (2) the short-term and long-term delayed recall score expressing recall memory; (3) the category-cued recall score; and (4) the recognition score. Considering that delayed recall memory is the first domain to be impaired in individuals with MCI (41), we will measure the changes in long-term delayed recognition scores in this study. The higher the score, the better the memory function.

The Montreal Cognitive Assessment-Basic (MoCA-B) scale will be used to evaluate the cognitive function of patients. The MoCA-B scale is an effective cognitive tool for detecting MCI among older Chinese individuals across all education levels (41). The MoCA-B assesses nine cognitive domains (executive function, language, memory, attention, orientation, calculation, concentration, conceptual thinking, and visual perception) with a total score of 30. The cut-off score for MCI is 16–22 for individuals with mid-level education and 17–24 for those with high-level education. The lower the score, the worse the cognitive function.

The FAQ will be used to evaluate the daily living ability of patients. It is a 10-item measure of difficulties in activities of daily living (42); each item is rated from 0 (no difficulty or independent) to 3 (dependent). The total severity (total sum score from all 10 items, range 0–30) reflects the extent of functional impairment. A total score > 9 indicates impairment of daily living ability; the higher the score, the lower the daily living ability.

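### The only test named for non-normal variables is the Mann–Whitney U test, which ignores the pairing if it is used for the planned within-group before-after comparisons

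*Protocol article*

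**What the plan says.** The protocol article, section 3.11 (Statistical analysis), lists the variables covered: "The measurement data includes various scale scores, indicators of brain function, DNA library of gut microbiota, and expression levels of inflammatory cytokines". For normally distributed variables it separates two situations. The independent-samples t-test serves comparisons between groups, and the paired-samples t-"test will be used for intra-group comparison". The next sentence deals with everything else: "The Mann–Whitney U test will be used for non-normal distributed variables". It does not limit that test to comparisons between groups. The Wilcoxon signed-rank test, or any other paired rank test, appears nowhere in the article.

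Before-after data on the same patients are central to the design. Section 3.8.1 says of the clinical scales: "These outcomes will be measured at baseline and after 12 weeks of the intervention". Table 1 schedules fMRI, blood and faeces at week 0 and week 12 as well. The abstract announces that "the changes in the AG and WG groups before and after treatment will be observed". The significance threshold is p < "0.05 will be considered the threshold for statistical significance". Section 3.5 fixes the size: "Thus, the sample size in our study will be 20 participants per group".

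**The concern.** The Mann–Whitney U test takes its null variance from two independent samples. Two values from one patient are usually positively correlated, so the difference between the two time points varies less than the test assumes. The test statistic is then too small and the p-value too large. The plan recognises the pairing for normal variables, where it chooses a paired t-test, but provides nothing equivalent for non-normal ones.

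What is at stake is the within-group reporting of any scale, cytokine, taxon or imaging measure that fails the normality check. With 20 patients per group, real changes over 12 weeks could go undetected for a reason that has nothing to do with the data. Two markers in one table could also be judged by different standards, one by a test that uses the pairing and one by a test that ignores it.

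**Working it through.** **Reproducing a stated figure.** There is none to reproduce. The 20 per group in section 3.5 rests on precedent from similar studies, without an effect size, SD or power.

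**Inputs from the article.** 20 pairs per within-group test (section 3.5), and a threshold of 0.05 (section 3.11; two-sided is assumed, since sidedness is not stated).

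**Assumed inputs.** The article gives neither the before-after correlation ρ nor the size of change. I take ρ = 0, 0.3, 0.5 and 0.7 on the log scale, log-normal values, and a shift of either 0 or 0.5 SD on the log scale.

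**Step 1: large-sample approximation of the type I error.** If both time points have the same distribution, the Mann–Whitney z-statistic computed on paired data has standard deviation of about √(1 − ρs) instead of 1, where ρs is the rank correlation. For bivariate normal logs, ρs = (6/π)·arcsin(ρ/2). The real rejection rate is therefore about 2Φ(−1.96/√(1 − ρs)).

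- ρ = 0.3: ρs = 0.288; 1.96/√0.712 = 2.32; rate about 2.0%.
- ρ = 0.5: ρs = 0.483; 1.96/√0.517 = 2.73; rate about 0.6%.
- ρ = 0.7: ρs = 0.683; 1.96/√0.317 = 3.48; rate about 0.05%.

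**Step 2: simulation at the actual size.** 20,000 simulated data sets per setting, 20 pairs, two-sided 0.05. Both tests use the normal approximation, and the signed-rank test is applied to raw log-normal differences.

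| Assumed ρ | Type I error, Mann–Whitney | Type I error, signed-rank | Power, Mann–Whitney | Power, signed-rank |
|---|---|---|---|---|
| 0 | 4.8% | 5.0% | 32% | 28% |
| 0.3 | 2.3% | 5.1% | 29% | 37% |
| 0.5 | 0.9% | 4.9% | 27% | 48% |
| 0.7 | 0.1% | 4.8% | 24% | 68% |

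Repeat simulations agree to within about one percentage point. At ρ = 0.7 the Mann–Whitney type I error lies between 0.1% and 0.2%. The exact figures exceed the Step 1 approximation slightly, as expected with only 20 pairs, and the direction is the same.

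**Step 3: sensitivity.** If the signed-rank test is applied to logged values, its power rises to 42%, 54% and 76% at ρ = 0.3, 0.5 and 0.7. The Mann–Whitney figures do not change, because its ranks are unaffected by taking logs. At ρ = 0 the problem vanishes, but zero correlation between two measurements on one patient is implausible.

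**Step 4: where the rule does no harm.** Patients in the acupuncture and waiting-list groups are different people, so Mann–Whitney is valid for comparing them, whether on week 12 values or on change scores. The same holds for patients against healthy volunteers.

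**The case against.** The strongest defence is one of wording. The sentence in section 3.11 does not mention within-group use, and a condensed article may simply have named the between-group rank test and left the paired one to a fuller document. That is fair as to intent: a reader might infer that the plan expressly prescribes Mann–Whitney for before-after data, and the text does not go that far. The point still stands. The sentence is unrestricted, it directly follows one that defines both kinds of comparison, and no paired alternative is given. If only between-group use was meant, non-normal within-group comparisons have no test at all, and the sentence needs the same correction.

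A reader might also infer that the trial's main result is compromised. It is not. The primary outcome is the change in ADAS-cog, and its randomised comparison can validly use Mann–Whitney on change scores.

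Nor does the article support saying that the faulty rule would govern most of the mechanistic work. Section 3.8.3 compares gut flora between the two randomised groups, the Discussion describes changes between those groups and differences from healthy volunteers, and the correlation analysis uses multiple linear regression. Which variables will prove non-normal is not known from the article; that cytokines, taxa and low-scoring scales are candidates is an expectation.

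Finally, the error is conservative under positive correlation, so it does not create false claims of within-group benefit. All of these limits hold. They lower the severity but do not remove the fault.

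**Conclusion.** The point holds in a limited form. Section 3.11 plans within-group before-after comparisons but, for non-normal variables, names only a test for independent samples. Used as written on 20 pairs, that test works at well below its nominal 5% level. It gives up about 8 percentage points of power at ρ = 0.3 (29% against 37%) and about 44 points at ρ = 0.7 (24% against 68%). These sizes rest on assumed correlations, a log-normal shape and a shift of 0.5 SD on the log scale, none of which the article supplies. The direction needs only that the pairs are positively correlated.

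The fault is confined to within-group tests of variables that prove non-normal. Severity is minor to moderate: the consequence is missed within-group changes, and comparisons between different groups of people are untouched.

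**What to change.** Replace the sentence in section 3.11 with: *For non-normal variables, the Mann–Whitney U test will be used for inter-group comparison and the Wilcoxon signed-rank test for intra-group (before-after) comparison.*

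The cost is one sentence. It needs no new data, no change of design and no other software, since SPSS provides the signed-rank test. It should be made before the data are analysed, so that the choice of test cannot depend on results. Log-transforming skewed markers and keeping them in a parametric framework, such as the paired t-test or ANCOVA, is an option but is not needed to cure this fault.

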**Discussion:**

This study will identify the efficacy and provide preliminary data on the possible mechanism of acupuncture in treating aMCI. Furthermore, it will also identify biomarkers of the gut microbiota, inflammatory cytokines, and brain function correlated with therapeutic effects. The results of this study will be published in peer-reviewed journals.

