## Objectives

2.

To observe the efficacy and safety of acupuncture in patients with aMCI;To investigate whether acupuncture can regulate brain function by affecting the gut microbiome and expression of inflammatory cytokines in the gut-brain axis, thus playing a role in improving cognitive function in patients with aMCI.

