### Trial design and setting

3.1.

This is a parallel-designed, prospective, assessor-blinded multicentre (*n* = 4) randomised controlled study to explore whether acupuncture can improve clinical symptoms of patients with aMCI by regulating the gut-brain axis. Forty patients with aMCI will be randomly and evenly assigned to either the acupuncture group (AG) or the waiting-list group (WG). Various scales will be assessed, functional Magnetic Resonance Imaging (fMRI) scans will be performed, and blood and faeces samples will be collected from both groups of patients before and after the intervention. In addition, 20 healthy participants will be recruited as normal control, and relevant tests and examinations will be conducted at enrollment. Cognitive-related scale, daily-living ability scale, emotion scale, mental behaviour scale and sleep scale will be used to observe the changes in clinical symptoms of patients with aMCI and to identify the therapeutic effect of acupuncture on aMCI. The gut-brain interaction characteristics of patients will be determined, and the regulatory effect of acupuncture on gut microbiota, inflammation cytokines and brain function will be explored. Subsequently, the correlation analysis of clinical efficacy can be related to gut microbiota composition, inflammation cytokines and brain function. The flow chart of trial procedures is displayed in Figure 1, and the study schedule is depicted in Table 1. The trial will be conducted at four sub-centres (West China Hospital of Sichuan University, Sichuan Provincial People’s Hospital, Chengdu Fourth People’s Hospital, and Sichuan Provincial Rehabilitation Hospital). The study protocol reporting follows the Standard Protocol Items: Recommendations for Interventional Trials (SPIRIT) guidelines and checklist (32).

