This is the first randomised trial to integrate acupuncture into the gut-brain axis in patients with aMCI. Brain function, gut flora, and neuroinflammatory cytokines are indicators of functioning of the gut-brain axis. The differences in the above indicators between patients with aMCI and healthy individuals will be identified to determine gut-brain interaction characteristics in patients with aMCI. Additionally, changes in these indicators between the AG and WG before and after treatment will also be investigated to illustrate the potential mechanism of acupuncture’s therapeutic effects on patients with aMCI. The main advantage of this study is the collection and evaluation of multifaceted data. We hypothesise that acupuncture therapy can improve clinical symptoms in patients with aMCI by regulating the gut-brain axis. If the hypothesis is proven, acupuncture therapy would not only serve as a novel alternative approach for treating aMCI, but also offer new information to further clarify the mechanism of the effects of acupuncture.

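### The mechanism objective describes a mediated effect, but the only stated analysis linking markers to efficacy is a correlational regression whose listed variables do not include arm

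*Protocol article*

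**What the plan says.** All references are to the protocol article.

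- **Objective.** Section 2, second objective: "To investigate whether acupuncture can regulate brain function by affecting the gut microbiome and expression of inflammatory cytokines in the gut-brain axis", and thereby improve cognition.
- **Hypothesis and intended conclusion.** Section 4 (Discussion), last paragraph: "We hypothesise that acupuncture therapy can improve clinical symptoms in patients with aMCI by regulating the gut-brain axis". The next sentences go further: "If the hypothesis is proven, acupuncture therapy would not only serve as a novel alternative approach for treating aMCI".
- **Analysis.** Section 3.11: "The correlation analysis between clinical efficacy, gut microbiota, inflammatory cytokines, and brain function will be conducted using multiple linear regression analysis". The threshold p < 0.05 "will be considered the threshold for statistical significance". The sentence lists four families of variables and arm is not one of them. No indirect-effect analysis is named. The Abstract places this correlation in patients with aMCI, without separating the arms.
- **Markers.** Section 3.8.4 names eight serum proteins. Sections 3.8.2 and 3.8.3 add fMRI and metagenomic measures without a count.
- **Timing.** Table 1 schedules markers and outcomes for the patients at week 0 and week 12 only.
- **Size.** Section 3.5: "Thus, the sample size in our study will be 20 participants per group", chosen by precedent from imaging and mechanism studies.
- **Softer wording elsewhere.** The Abstract says the study will "provide preliminary data on the possible mechanism of acupuncture in treating aMCI", and the opening of section 4 speaks only of exploring the relationship.

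**The concern.** A mediated effect has two links: arm changes the marker, and the marker changes the outcome at a given arm. A regression of efficacy on markers in pooled patients estimates neither link cleanly. Three situations produce the same significant coefficient:

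1. true mediation;
2. a common effect of arm, where acupuncture moves marker and outcome by separate routes;
3. prognosis, where the marker predicts outcome but acupuncture does not touch it.

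The second is a bias that grows with the effect of acupuncture. The more acupuncture does, the more unrelated markers would appear to explain it. What is at stake is the mechanistic conclusion and the list of markers reported as tied to therapeutic benefit.

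**Working it through.** **Plan's own figure.** There is none to reproduce. Section 3.5 gives no effect size, SD or power, and nothing in it is sized for the regression.

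**Inputs.** From the document: 40 patients, 20 per arm (sections 3.1 and 3.5); threshold 0.05 (section 3.11; two-sided assumed, as sidedness is not stated); eight serum markers (section 3.8.4). Assumed: shifts of 0.5 to 1.2 SD, normal errors with within-arm SD of 1, and marker and outcome independent within arm.

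**Step 1: correlation created by arm alone.** With 1:1 allocation and a shift of d SD in both marker and outcome, the arm contributes d²/4 to each variance and to the covariance. The pooled correlation is therefore

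r = (d²/4) / (1 + d²/4).

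- d = 0.5: 0.0625 / 1.0625 = 0.06
- d = 0.8: 0.16 / 1.16 = 0.14
- d = 1.0: 0.25 / 1.25 = 0.20
- d = 1.2: 0.36 / 1.36 = 0.26

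**Step 2: how often it is called significant.** Simulation, one marker, no mediation, 5,000 trials per row:

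| Shift in marker and outcome | Without arm | With arm |
|---|---|---|
| 0.5 SD | 7.2% | 5.2% |
| 0.8 SD | 13.4% | 4.5% |
| 1.0 SD | 23.7% | 5.0% |
| 1.2 SD | 39.6% | 5.1% |

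Hand check at d = 1.0 by Fisher's z: atanh(0.20) × √37 = 0.203 × 6.08 = 1.23, and P(Z > 1.96 − 1.23) is about 0.23, in line with the simulated 23.7%.

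**Step 3: several markers.** Eight independent tests at 0.05 under a complete null: 1 − 0.95⁸ = 0.337. If arm shifts all eight markers and the outcome by 0.8 SD with no link (2,000 trials), at least one false link appears in 64% of trials (markers one at a time) or 42% (one joint model) without arm. With arm the figures are 34% and 30%. The arm term removes the bias; what remains is multiplicity, which needs its own control.

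**Step 4: prognosis read as mechanism.** A marker that acupuncture does not affect, but that predicts the outcome (assumed slope 0.5, arm effect on outcome 0.8 SD), is significant in 78% of trials in the regression without arm. An arm term would not remove this association, because it is real; it is simply not mediation.

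**Step 5: what a proper mediation test could do here.** Requiring both links to be significant, with arm in the outcome model, power for one marker at N = 40 is 13% (arm-to-marker effect 0.5 SD, marker-to-outcome slope 0.3), 43% (0.8, 0.39), 57% (0.8, 0.5), 64% (0.8, 0.59) and 73% (1.0, 0.5). It stays below 80% in every scenario tried.

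**The case against.** **The model terms may be set elsewhere.** Section 3.11 names a method family in one sentence, and an analysis plan that is not shown may add arm. A reader might infer that arm is deliberately excluded. The document does not say so: arm is absent from the listed variables, but covariates are not listed at all. The rates in the table hold only if the regression is run on pooled patients as listed. If it were run within one arm, arm could not create the correlation, but only 20 patients would remain. This limits the claim without removing it, because adding arm would still leave a correlational method facing a mediation objective.

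**Too many markers for 40 patients.** A reader might infer a saturated model. Only eight markers can be counted, and eight predictors in 40 patients leave 40 − 8 − 1 = 31 residual degrees of freedom, so that model can be fitted. Nothing says that taxa and brain indices all enter one model. Nor does inflated R² matter for the stated criterion, since the p-values allow for the number of predictors. Multiplicity is the relevant issue.

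**The analysis is secondary and hedged.** This is largely right. The primary outcome is change in ADAS-cog, the first objective is efficacy and safety, and the markers are also compared between randomised arms. A reader might infer that the trial's main result rests on this regression; it does not. But the between-arm comparison tests only the first link, and the hedges in the Abstract and at the start of section 4 are not carried into section 2 or the end of section 4.

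**Timing is a design limit.** True. No reanalysis, including the one proposed here, resolves direction from two visits.

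**Conclusion.** The point holds as a mismatch between objective and method. The regression, applied as listed to the pooled patients, cannot tell mediation from a common effect of arm or from prognosis. The false-link rate for one marker is about 7% to 40% over assumed shifts of 0.5 to 1.2 SD, against about 5% with an arm term. At the small end the bias is slight, and no shift size is given in the document. The 34% figure for eight markers assumes independence and testing at 0.05 each. The absence of arm is read from the list of variables, not from an explicit statement. The change is worth making because it removes a specific bias at almost no cost. It does not touch the primary ADAS-cog comparison.

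**What to change.** 1. In section 3.11, replace the regression sentence with: change in ADAS-cog regressed on change in marker, with arm, baseline ADAS-cog and baseline marker as covariates, one marker per model.
2. Name a short list of markers in advance (for example one diversity index, the eight serum proteins and one connectivity measure) and control the false discovery rate across it.
3. If an indirect effect is reported, give it with a bootstrap confidence interval and label it exploratory. Step 5 shows why it should not be treated as a confirmatory test.
4. Reword the second objective in section 2 and the closing conditional in section 4 as exploratory association, matching the Abstract and the opening of section 4. Add that direction cannot be established, because markers and outcomes share the same two visits.

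The cost is a little more analysis, some wording, and a weaker mechanistic claim. No visit, sample or procedure changes.
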